**Figure 4 figure4:**
[figure not shown]
Trial flow.

### Data Analysis

#### Assessment of the Scale Quality

Before conducting any analyses, we will assess the scale quality of all measurement instruments where appropriate, following the 2 steps proposed by Crutzen and Peters [62]: (1) conformation of intended structure of the measurement instrument by means of exploratory factor analyses and (2) calculation of omega [63] as a less biased alternative to (Cronbach) α. Compared to α, omega has more realistic assumptions regarding variances of and covariance between items [64]. Omega_hierarchical_ is based upon the sum of the squared loadings of items on the general factor and reduces the risks of misjudging the internal consistency of scientific scales [65]. Values will be calculated with R [66], making use of the integrated development environment RStudio [67].

#### Analysis of Primary and Secondary Outcomes

To assess the effects of the DA on dichotomous and continuous (primary and secondary) outcome measures, logistic and linear regression analyses will be conducted, respectively. Mediation analyses will be conducted to determine whether the effects of the DA on smoking abstinence are mediated through cessation assistance use. All analyses will include covariates that were selected a priori (as recommended by Gruijters [68] and De Boer et al [69]), if these are also associated with the 3 outcome measures as described in our hypotheses (ie, smoking abstinence, evidence-based cessation assistance use, and decisional conflict) within our sample. Demographic factors (ie, age, gender, and education) were selected for all 3 outcome measures. The Revised Fagerström Test for Nicotine Dependence was also selected for the smoking-related outcome measures, whereas stage of decision making was selected for decisional conflict. More information on the rationale for selecting those covariates can be found in Multimedia Appendix 1*.* Results will be reported from both the fully adjusted as well as crude analyses [68]. These analyses as well will be done with R [66], making use of the integrated development environment RStudio [67]. To test the robustness of the results, all analyses will be conducted according to 3 different approaches (if applicable): analyses based on (1) worst case scenario (dropout respondents are considered not to have changed), (2) multiple imputations, and (3) complete cases only. We will also test whether selective dropout has occurred in order to subsequently minimize the bias that this can cause.

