Based on these limitations and the existing literature, an online DA, called “VISOR,” containing an explicit evidence-based VCM and tailored advice was developed that helps smokers to choose evidence-based cessation assistance tools. This DA was systematically developed and is currently being tested in a national randomized controlled trial (RCT) for its effect on individual decisional processes and smoking cessation attempts, as well as smoking abstinence compared to a DA without the explicit VCM component. Specifically, we aim to test the following hypotheses. 

H_1a/b/c_ is that a DA with an explicit VCM and tailored advice will lead to a statistically significant increase in smoking abstinence after 1 month (H_1a_), 6 months (H_1b_), and 12 months (H_1c_) compared to a DA without an explicit VCM and tailored advice: direct effect on smoking abstinence.

H_2a/b/c_ is that a DA with an explicit VCM and tailored advice will lead to a statistically significant increase in evidence-based cessation assistance use after 1 month (H_2a_), 6 months (H_2b_), and 12 months (H_2c_) compared to a DA without an explicit VCM and tailored advice.

H_3a/b_ is that the positive effect of a DA with an explicit VCM and tailored advice (vs a DA without an explicit VCM and tailored advice) on smoking abstinence after 6 months and 12 months will be at least partially mediated by the use of evidence-based cessation assistance at 1-month (H_3a_) and 6-month (H_3b_) follow-ups, respectively: indirect effect on smoking abstinence.

H_4_ is that a DA with an explicit VCM and tailored advice will lead to a statistically significant decrease in decisional conflict (state of uncertainty about which course of action to take) right after the DA compared to a DA without an explicit VCM and tailored advice.

In addition, it will also be tested whether the DA is more cost-effective compared to a DA without the explicit VCM component. This paper aims to thoroughly describe the DA “VISOR,” its development process, and the study protocol to test its (cost-)effectiveness.

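### Covariates named in advance enter the adjusted models only if they prove associated with the outcomes in the trial's own data, so those models are not fully pre-specified

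*Protocol article*

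**What the plan says.** The section Analysis of Primary and Secondary Outcomes begins with a commitment: "All analyses will include covariates that were selected a priori". The same sentence then adds a condition: "if these are also associated with the 3 outcome measures as described in our hypotheses". It lists the three outcomes and closes with the data on which the condition is judged: "evidence-based cessation assistance use, and decisional conflict) within our sample".

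The candidates are a short closed list. "Demographic factors (ie, age, gender, and education) were selected for all 3 outcome measures". FTND-R is added for the smoking-related outcomes, "whereas stage of decision making was selected for decisional conflict". All of them are collected at baseline (Table 3, t=0), where they are listed as covariates in the main analyses without any condition.

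Three other statements bear on the point:

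- Both versions of each model are shown: "Results will be reported from both the fully adjusted as well as crude analyses".
- Robustness is to be judged by repetition: "all analyses will be conducted according to 3 different approaches (if applicable"), namely worst case, multiple imputation and complete cases.
- Abstinence is tested at three times: "increase in smoking abstinence after 1 month (H_1a_), 6 months (H_1b_), and 12 months (H_1c"). Assistance use (H2) is tested at the same three times, and H3 concerns mediation by assistance use.

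**The concern.** Choosing covariates in advance is meant to fix the model before anyone sees outcomes. A second filter based on observed association with the outcome removes part of that protection: the pool is fixed, but the fitted model is not. This is a rule that the article states, not a detail left to an analysis plan.

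Three things are at stake.

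1. **Pre-specification.** The rule covers all analyses, so it reaches the primary outcome, 7-day point prevalence abstinence.
2. **Comparability.** An odds ratio from a logistic model depends on what it is conditioned on. If the retained set changed between the three missing-data approaches, a difference between them would mix the missing-data assumption with the covariate set.
3. **Mediation.** Use of cessation assistance is not randomised. In the H3 models, covariates are there to control confounding between mediator and outcome. A confounder such as nicotine dependence that misses a threshold by chance would be left out, and the indirect effect could be biased. Randomisation of the decision aid does not protect against this.

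**Working it through.** **1. The plan's own figure.** Inputs from Required Sample Size: 20.2% vs 13.6%, one-sided α = 0.05, power 0.80. The mean rate is (0.202 + 0.136)/2 = 0.169.

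n per arm = [1.645·√(2·0.169·0.831) + 0.842·√(0.202·0.798 + 0.136·0.864)]² / 0.066² = 397.6, rounded up to 398.

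That gives 796 in total, and 796/0.5 = 1592 at baseline. The stated figures reproduce. The calculation is unadjusted, so the covariate rule does not enter it.

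**2. How easily a real predictor fails a screen.** The article gives no covariate effects and no screening threshold, so the odds ratio (OR) per SD and the two-sided p<0.05 criterion here are assumptions. The approximate SE of a log OR per SD is 1/√(n·p·(1−p)).

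| Setting | SE | Chance of p<0.05, OR 0.80 per SD | Chance of p<0.05, OR 0.85 per SD |
|---|---|---|---|
| 796 completers, 16.9% abstinent | 0.0946 | \|ln 0.80\|/SE = 2.36, about 66% | about 40% |
| 1592 randomised, dropouts counted as smokers, 8.45% abstinent | 0.0901 | \|ln 0.80\|/SE = 2.48, about 70% | about 44% |

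A genuine predictor of modest strength could thus be dropped in roughly 30% to 60% of trials of this size.

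**3. Simulation.** Set-up: 1592 randomised, a random half observed, four candidate covariates, outcomes at three times correlated within person, a univariable screen at p<0.05, 1500 runs per scenario. Assumed absolute log odds per SD were 0.05-0.2 (weak), 0.1-0.35 (middle) and 0.2-0.5 (strong). The treatment log OR was 0 or 0.475 (OR 1.61, as implied by 20.2% vs 13.6%). Tests are one-sided at 5% on completers at one time point.

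| Scenario | Type I error: crude / all covariates / screened | Power: crude / all covariates / screened | Set differs across 3 times | Set differs, complete case vs worst case |
|---|---|---|---|---|
| Weak | 4.9 / 4.4 / 4.9% | 78.6 / 78.6 / 78.4% | 72-74% | 18-20% |
| Middle | 4.5 / 4.6 / 4.6% | 78.9 / 79.8 / 79.5% | 78% | 22-23% |
| Strong | 4.1 / 4.3 / 4.2% | 78.6 / 81.7 / 81.4% | 82-84% | 24-26% |

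The Monte Carlo standard error is about 0.6 points for type I error, √(0.05·0.95/1500), and about 1.0 point for power, √(0.8·0.2/1500). Screening does not inflate type I error. It costs 0.2 to 0.3 points of power against always adjusting. The last two columns apply only if the screen is repeated for each analysis.

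**4. How far the odds ratio moves.** The marginal OR is (0.202/0.798)/(0.136/0.864) = 1.608. Conditioning on one normal covariate with OR 0.80 per SD gives 1.613; on four independent ones, 1.630. With OR 0.85 per SD, one covariate gives 1.611. The shift is real but small.

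**5. Mediation.** The documents give no mediator-outcome association, so no size can be put on the possible bias. The argument is structural: the sentence on covariates directly follows the one announcing the mediation analyses and applies to all analyses.

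**The case against.** The strongest reply is that this does little harm. The list is closed and short. Baseline covariates are balanced by randomisation in expectation, so dropping one does not confound the randomised comparison. Error rates and power barely move, the odds ratio changes only in the second or third decimal, and the crude analysis, which involves no selection, is always reported. All of this stands for H1, H2 and H4. It does not cover H3, where the mediator is not randomised and a crude model offers no remedy.

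A reader might infer that the covariate set will differ across time points and missing-data approaches. The article does not say so. It ties the check to the three outcome measures, and one check per outcome, carried through all analyses, fits the wording equally well. The 72-84% and 18-26% figures therefore describe one possible reading. A single check would still use trial outcome data.

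A reader might also infer that the nominal error rate is compromised or that much precision is lost. The simulation does not support either.

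Multimedia Appendix 1 is not shown and may give a criterion for association. It is cited for the rationale of the selection, and a criterion would not remove the in-sample condition. Which of the crude and adjusted models leads is a separate matter that an analysis plan may settle.

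**Conclusion.** The point holds in a limited form. The adjusted models are selected in part on trial outcome data, despite being described as chosen in advance, and this reaches the primary outcome and the mediation analyses. The consequences to weigh are lost pre-specification, possible loss of comparability between analyses if the check is repeated, and possible bias in the indirect effect.

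For the randomised comparison the expected effect is small: one-sided type I error of 4.2-4.9% and less than one point of power. Those figures rest on assumed covariate effects, a p<0.05 screen and dropout completely at random, none of which is in the documents. The change is worth making because it is free, not because the main result is in danger.

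**What to change.** Delete the condition that makes inclusion depend on association in the sample. State instead that every adjusted model contains the covariates named for its outcome, whatever their observed association: age, gender and education throughout, FTND-R for the smoking-related outcomes, and stage of decision making for decisional conflict. Apply this at every time point, under every missing-data approach, and in the mediation models.

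The cost is one clause. All the covariates are already collected at t=0. The sample size stays at 398 per arm, 796 in total and 1592 at baseline. About 135 abstinent participants are expected among completers (796 × 0.169), which is ample for a handful of covariate terms.

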### Study Population

Recruitment is predominantly conducted online to reflect the online nature of the DA. We make use of various methods: Mainly, we are recruiting participants through project social media accounts (eg, [28]) and paid social media advertisements. We decided to make use of 4 big social media platforms (ie, Facebook, Instagram, Twitter, and LinkedIn) as they cater to different target groups [29]. In addition, our recruitment messages are being shared on the social media accounts of the project members and their institutions. Also, we promote the RCT through the project’s website, and we asked various relevant Dutch institutes and organizations (eg, the Dutch institute for addiction and mental health and municipal health services) to promote the study. Finally, we advertise the study in online newspapers. All recruitment materials include a link to enroll in the RCT, if possible, to simplify the process for potential participants as much as possible. Study inclusion criteria are: (1) participants are currently smoking, (2) participants are motivated to stop smoking within 6 months, (3) participants are 18–100 years old, (4) participants are able to understand Dutch, and (5) participants have access to the internet and have the necessary internet literacy skills to use the intervention. People are excluded if they only use e-cigarettes; however, dual users can participate. The rationale behind the inclusion and exclusion criteria is described in Table 1.

**Table 1 table1:** Overview of the randomized controlled trial inclusion and exclusion criteria, including rationale.

Criteria			Rationale

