### Required Sample Size

The power calculation was based on the dichotomous outcome measure of smoking abstinence (primary outcome: 7-day point prevalence abstinence). The only previous RCT in the Netherlands testing the effect of a DA for smoking cessation on this outcome measure showed a significant effect (20.2% vs 13.6%) at 6 months [14]. To be able to significantly (α=.05; β=.20) detect the same effect in a 1-sided test, 398 smokers per arm are necessary at the end of the trial (796 in total). Considering 50% attrition over the intervention period, we aim to include 1592 smokers at baseline.

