**Follow-up (t=4): 12 months after baseline**			
	Decision implementation	Implemented decision (choice) after having used the DA	Hypothesis testing, H_2c_
	Smoking (cessation) behavior	Prolonged abstinence; 7-day point prevalence abstinence; for users that did not successfully stop: type of tobacco products and amount of tobacco consumption [52]	Hypothesis testing, H_1c_ and H_3b_ (7-day point prevalence abstinence [52]); additional studies (see “Data Analysis”)
	Productivity loss	iPCQ [54]	Economic evaluation
	Health care utilization	Contacts with health care professionals (plus frequency) in the past 6 months, cessation assistance utilization (plus frequency) in the past 6 months [55]	Economic evaluation
	Quality of life	ICECAP-A [56]	Economic evaluation
	Decisional regret	Decision regret scale [61]	Additional studies (see “Data Analysis”)
	Evaluation questions	Regarding perceived decision support	Process information

^a^N/A: not applicable.

Participants are invited to fill in each follow-up questionnaire if they made use of the entire DA, even when they skipped one of the other follow-up questionnaires. To avoid high drop-out rates, participants receive either 1 automatic reminder after a week (if they have not filled in the follow-up questionnaires at all) or 2 after 2 days and a week (if they already started filling in at least parts of the follow-up questionnaires). Participants that started using either the DA or started filling in the baseline questionnaire (t=0) without finishing it also receive 2 automatic reminders (after 2 days and a week). In addition, participants who took part in the last measurement receive €10 (US $11.84). A visual representation of the trial flow can be seen in Figure 4.

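### The no-change rule for dropouts is not a worst case for the H3 mediation analyses: under overlapping dropout it can create a use–abstinence link and a false mediated effect

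*Protocol article*

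**What the plan says.** The section Analysis of Primary and Secondary Outcomes plans the mediation work: "Mediation analyses will be conducted to determine whether the effects of the DA on smoking abstinence are mediated through cessation assistance use". The same paragraph then says that, to test robustness, "all analyses will be conducted according to 3 different approaches (if applicable"). The three are the "worst case scenario (dropout respondents are considered not to have changed"), multiple imputation, and complete cases. None is named as the main approach, and mediation is not exempted.

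H3, in the Introduction, concerns an effect on abstinence at 6 and 12 months that is "mediated by the use of evidence-based cessation assistance at 1-month (H_3a_) and 6-month (H_3b_) follow-ups, respectively". Table 3 shows that use and abstinence both come from the follow-up questionnaires.

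Three other statements bear on the point:
- Study Population requires that "1) participants are currently smoking", so an unchanged participant is a smoker.
- Required Sample Size expects heavy loss: "Considering 50% attrition over the intervention period".
- Trial Flow and Measurement Instruments invites those who used the entire DA to every follow-up, "even when they skipped one of the other follow-up questionnaires".

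**The concern.** For the comparison of arms on abstinence (H1), counting dropouts as smokers is the usual cautious choice. In H3 the same rule fills in two variables for the same person. If the mediator is set to no use and the outcome to smoking, everyone absent at both waves lands in one cell of the use-by-abstinence table. Recorded use and recorded abstinence are then both markers of having responded, and they become associated even if use does nothing for abstinence.

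H3 is a named hypothesis and the trial's account of how the DA works. If the arms also differ in coded use, the product of the two paths can be declared a mediated effect that does not exist. A result labelled worst case would then appear to support the hypothesis.

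**Working it through.** **The plan's own figure.** For 20.2% vs 13.6%, one-sided α = 0.05, power 80%, with pooled variance under the null:

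n = [1.645·√(2·0.169·0.831) + 0.842·√(0.202·0.798 + 0.136·0.864)]² / 0.066² = 398 per arm.

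This gives 796 in total, and 796/0.5 = 1592 at baseline. The stated sample size reproduces. The simulations below use 796 randomised per arm.

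**Inputs.**
- From the article: 50% attrition; abstinence of 20.2% and 13.6%, mean 16.9%.
- Assumed, because the article gives no figure: the proportion using assistance, the pattern of dropout by wave, and dropout unrelated to use and abstinence.
- Assumed reading of the rule: unchanged means no use and smoking.

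**Induced link, same people missing at both waves.** Let r be the proportion responding, m the proportion using assistance and y the proportion abstinent, with use and abstinence independent (true OR 1.0). After coding:

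- P(abstinent | use) = y
- P(abstinent | no use) = r(1−m)y / (1−rm)

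With r = 0.5, m = 0.4, y = 0.20: 0.20 against 0.5·0.6·0.20/0.80 = 0.075. OR = (0.20/0.80)/(0.075/0.925) = 3.08. The same inputs give OR 2.39 at 40% dropout and 1.89 at 30%.

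With r = 0.5, m = 0.3, y = 0.169: 0.169 against 0.5·0.7·0.169/0.85 = 0.070. OR = 2.72.

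**Induced link, general pattern.** Let r₂ be response at the mediator wave, g response at the outcome wave among mediator-wave responders, and h response at the outcome wave among mediator-wave non-responders:

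- P(abstinent | use) = g·y
- P(abstinent | no use) = y[r₂(1−m)g + (1−r₂)h] / (1−r₂m)

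With y = 0.169:

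| Pattern | OR at m = 0.3 | OR for m from 0.2 to 0.5 |
|---|---|---|
| Same 50% missing at both waves | 2.72 | 2.50–3.41 |
| 30% out at mediator wave, 50% at outcome wave, none return | 1.70 | 1.61–1.98 |
| 40% out at mediator wave, one fifth of them return, 50% missing at outcome wave | 1.61 | 1.55–1.78 |
| Missingness at the two waves independent | 1.00 | 1.00 |

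**False mediated effect.** Simulated trials with no effect of use on abstinence; a mediated effect is declared when both paths are significant.

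| Setting | No-change rule | Complete cases |
|---|---|---|
| Use 30% vs 40%, same 50% missing | 82% | 4% |
| Use 30% vs 40%, 30% then 50% missing | 81% | 4% |
| Use 30% vs 40%, 40% out with some returning | 68% | 4% |
| Use 40% vs 50%, same people missing both waves | 69% | 2.3% |
| Use 40% vs 50%, partly overlapping | 75% | 1.0% |
| No effect on use, equal dropout | 5% | under 1% |
| No effect on use, dropout 55% control vs 45% intervention | 52% | under 1% |
| Use effect present, independent missingness | about 2–3% | 4% |

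The 40% vs 50% rows use two-sided 5% tests on each path and the other rows one-sided 5% tests, except that the last row's no-change range covers runs of both kinds. For the first three rows, judged instead by whether a 95% interval for the product excludes zero, the rule gives 73%, 67% and 50%. With a 5-point effect on use, joint significance is about 25%. Reversing the dropout imbalance gives an interval wholly below zero in 39% of trials.

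**Carrying baseline use forward.** Table 3 records assistance use in the 6 months before baseline, so unchanged could mean that value. With the 10-point use effect, joint significance falls to 47% if 20% used assistance at baseline, and to 4% if 40% did.

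**The case against.** The strongest reply concerns what the article commits to. The rule is one of three robustness runs. The other two do not build in this artefact, so a spurious H3 result would stand beside results that contradict it, and a check for selective dropout is also planned. The words "if applicable" leave room to exempt mediation. All of this limits the damage. But the exemption is not made, the rule can be computed for H3, and with no main approach named, conflicting H3 results have no stated resolution.

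The second reply concerns size, and much of it stands. Four stronger readings are tempting but not supported:

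- *The rule always favours H3.* It does not. With no arm difference in coded use there is no inflation, and with more dropout in the intervention arm the bias is negative. The 65–80% figures largely reflect power to detect an assumed 10-point effect on use.
- *Half the data set becomes non-users who smoke.* The 50% attrition is set against the number needed at the end of the trial, whereas H3a uses months 1 and 6. Only people absent at both waves are filled in on both variables, and participants may return after a missed wave.
- *The article codes dropouts as non-users.* It says only that they have not changed. Non-use is the natural reading but remains an inference.
- *The simulations describe H3 exactly.* H3 presupposes a positive effect on abstinence, and the tabulated runs have none. Requiring a significant total effect as well cuts the false rate to about 4%. If the article's 20.2% vs 13.6% is a purely direct effect, however, the rate with that requirement is about 52–62%. The spurious indirect effect itself averages only about 0.3–0.6 percentage points.

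Substantial overlap is nevertheless plausible. Only those who used the entire DA are invited to follow-up, and Results reports 519 finishers among 1248 accounts. If non-finishers count as dropouts, which the article does not say, they miss every wave. Some may also be ineligible or still in progress.

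**Conclusion.** The concern holds in conditional form. Applied to H3 as written, the no-change rule is not a worst case, because it can favour the hypothesis. Three conditions are needed for a false mediated effect: dropouts coded as non-users, the same people missing at mediator and outcome waves, and arms that differ in coded use through a real H2 effect or unequal dropout. The protocol itself hypothesises the H2 effect and expects 50% attrition.

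Under those conditions the induced odds ratio is about 1.6–3.1, depending on overlap. The false-positive rate for mediation is roughly 65–80% with a 10-point use effect and about 25% with a 5-point effect. With no arm difference in coded use it is about 2–5%. The comparison figure of 1–4% for complete cases is valid only when dropout is unrelated to use and abstinence. Carrying baseline use forward weakens or removes the inflation, but a value from before the DA is not a valid post-DA mediator.

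A reader might infer that the H1 arm comparison is affected too. This point gives no support for that. H3 is not the primary outcome, and the matter should be settled before its analyses are run.

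**What to change.** Add one sentence to Analysis of Primary and Secondary Outcomes stating that the no-change approach is not used for H3. Base H3 on the multiple imputation already planned, imputing use and abstinence jointly with arm, baseline data and the other waves in the imputation model. Report complete cases as the sensitivity analysis. The rule can stay for the H1 arm comparison if wanted.

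No new data are needed. The cost is that sentence and one fewer robustness run for H3.
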